# Breast cancer PAINT: a first-in-human, dose-escalation study to determine the safety of Plasma Adjuvant INtra-operative Treatment in breast cancer patients

**DOI:** 10.1186/s12885-025-14153-5

**Published:** 2025-04-22

**Keywords:** Non-thermal plasma, Breast cancer, Intraoperative treatment, Local recurrence risk

## Abstract

**Background:**

Non-thermal plasma (NTP) refers to an ionized gas composed of ions, electrons and other reactive agents. The anticancer properties of NTP have been proven in vitro and in vivo. The 10-year local recurrence risk (LRR) in breast cancer patients after breast conservation therapy (i.e., lumpectomy, typically followed by radiation therapy) is still as high as 15–20%. NTP could be used to further treat the tumor bed to reduce the LRR.

**Methods:**

Our primary objective is to determine the safe and tolerable dose of NTP treatment following breast cancer lumpectomy. Our secondary objectives are to assess the safety and tolerability of NTP and to assess the cosmetic effects of NTP treatment in patients with breast cancer. Our exploratory objective is to assess the impact of NTP treatment on cancerous and normal tissues. Patients are followed for up to 3 months after NTP treatment. The patients are divided into 3 groups: group A (*n* = 3): NTP treatment of part of the tumor bed ex vivo. Group B (*n* = 3): NTP treatment of part of the tumor bed in situ (all treated tissues are removed for analysis). Group C (*n* = 6–24): dose escalation per “3 + 3 Design” up to a maximum dose level of 3. NTP treatment of part of the tumor bed in situ (the treated parts of the tumor bed will not be excised, except for a small portion for analysis).

**Discussion:**

The safety and tolerability of treatment will be evaluated by means of dose-limiting toxicity, adverse event (AE) and serious adverse event reports; physical examinations; and laboratory safety evaluations. AEs will be coded according to CTCAE v5.0. The results will be tabulated to examine their frequency, grade, and relationship to the study treatment. The results of laboratory assessments will be evaluated similarly. The number of patients with cosmetic alterations linked to NTP treatment and the type of alteration will be assessed through quality of life questionnaires (questions about breast appearance and texture) and through photo collection. This is the first clinical trial to study the safety and tolerability of NTP in an all-breast cancer patient cohort.

**Trial registration:**

Name of the registry: ClinicalTrials.gov. Trial registration number: NCT06222788. Date of registration: 01/15/2024. URL of trial registry record: https://clinicaltrials.gov/study/NCT06222788.

## Background

Surgery is one of the pillars of breast cancer treatment and can even be the only treatment needed in the management of early-stage breast cancer. In the last two decades breast-conserving surgeries (BCS) or lumpectomies have been used more often than radical mastectomies. BCS aim to remove as little tissue as possible to eliminate the tumor while preserving most of the breast. Indications for BCS include ductal carcinoma in situ and T1-2 tumors (if there are no contraindications to adjuvant radiotherapy (RT)) and small tumors that can be resected with clear margins. However, the ratio of tumor to breast size must be considered, and women with larger breasts may still be eligible for BCS despite a larger tumor. Absolute contraindications to lumpectomy include prior RT and inability to obtain clear margins [1]. The use of adjuvant radiotherapy has been proven to decrease the local recurrence risk (LRR) and increase overall survival [2–4]. During lumpectomies, RT is used to complement more conservative cancer surgeries to maintain high local control without resorting to complete mastectomy [5]. Adjuvant RT can be given intraoperatively or postoperatively. Intraoperative radiation consists of inserting a radiation device inside the surgical cavity, and radiation is applied over 20–50 min [6]. External beam radiation therapy is often used to supplement intraoperative radiation therapy. Adjuvant external beam RT is the most common standard form of radiation treatment used to reduce LRR. This treatment consists of treating the entire or a large volume of the breast with radiation therapy over 5–25 days of daily treatment. In this case, a large volume of normal tissue surrounding the surgical cavity is irradiated to annihilate microscopic tumor cells that may permeate centimeters from the visible tumor [7]. As the cancer cell load is highest in the peritumoral area [8, 9], it dictates the dose of RT needed to eradicate the last cancer cells to obtain local control. However, RT can be associated with cosmetic and local adverse events such as breast shrinkage, induration, telangiectasia and breast edema [10–13], as well as severe side effects, such as symptomatic rib fracture, symptomatic lung fibrosis, ischemic heart disease and an increased risk of secondary cancers [10, 11, 13–15]. Moreover, LRR is still as high as 12% for triple-negative breast cancer (TNBC) patients (within 7 years) [16]. Another current strategy for reducing LRR is to use cavity shave margins (i.e., to remove a larger margin of normal tissue from the tumor bed) [17–19]. Cavity shaving, while efficient at reducing the rate of positive margins and the need for re-excision, goes against the current efforts to remove as little normal tissue as possible and is not always desirable when the cavities are close to blood vessels or the chest wall [17].

Plasma is the fourth state of matter; it is a gaseous mixture of electrons, ions, radicals, radiation, etc. Non-thermal plasma (NTP) can be generated with the help of an electric field applied to a gas. The temperature of an NTP usually ranges between 27 °C and 77 °C [20]. When in contact with ambient air, NTP can produce a mixture of reactive oxygen and nitrogen species (RONS) [21, 22], which are cytotoxic to various cancer models [23, 24]. For the treatment of cancer, NTP can be applied directly to cells to increase intracellular RONS levels, inducing damage to DNA, lipids, and proteins, and preventing cell proliferation [25, 26]. The NTP source used for this trial is the convertible plasma jet (CPJ). It has been successfully tested in vitro [27, 28] and in vivo (*to be published*) on breast cancer and sarcoma cell lines.

We hypothesize that NTP could be used intraoperatively, immediately after lumpectomy, to treat the tumor bed. Direct treatment using an NTP jet (where the NTP is in direct contact with the cells) could lead to the killing of remaining cancer cells within and around the surgical bed. Reducing the tumor burden would allow for a reduction in the LRR. In previous clinical [29, 30] and in vivo [31, 32] studies, NTP has not been shown to be associated with any severe adverse events. NTP could therefore be used instead of or in combination with the current methods to reduce LRR, for example by decreasing the dose of RT needed to clear the tumor bed of microscopic tumor cells left after surgery. The intraoperative use of NTP would not be an extra step for the patient, as it would be administered by the surgeon during the surgery. Before that technology can be assessed for its clinical efficacy, the safety and toxicity of NTP produced by CPJ must be investigated in humans. Therefore, this trial aims to determine safe and tolerable CPJ treatment conditions following breast cancer lumpectomy.

## Methods and study design

This first-in-human study was approved by the University of Montreal Research Hospital (CHUM) Research Ethics Board (#23.167) in compliance with the Declaration of Helsinki.

### Objectives

Primary objective: To determine the safe and tolerable dose of NTP in patients with breast cancer.
Primary endpoint: Using a 3 + 3 dose escalation design up to a maximum dose of 3, a safe and tolerable dose of NTP in patients with breast cancer will be determined. The adverse effects of NTP produced by the CPJ will be assessed based on DLTs, AEs, physical exams, quality of life (QOL) questionnaires, and clinically significant changes in laboratory evaluations. The AEs will use the descriptions and grading scales found in the revised NCI Common Terminology Criteria for Adverse Events (CTCAE). This study will utilize CTCAE Version 5.0 for adverse event reporting. All patients that receive the treatment and complete the 1-week follow-up visit will be evaluated for acute toxicity. All patients who receive the treatment and complete the 3-month follow-up visit will be evaluated for long-term events.
Secondary objectives: To assess the safety and tolerability of NTP in patients with breast cancer and to assess the cosmetic effects of NTP treatment in patients with breast cancer.
Secondary endpoints: Number of patients with adverse events linked to NTP treatment and type of adverse event and number of patients with cosmetic alterations linked to NTP treatment and type of alteration. The adverse events of special interest (AESIs) will be assessed through QOL questionnaires (questions on breast appearance and texture) and through photo collection. The following AESIs will be recorded throughout the study:
Fatigue; grade 3,Breast pain; grade 3,Skin ulceration; grade 3,Chest wall necrosis; grade 3,Breast atrophy; grade 3,Change in breast texture,Cosmetic issues,Discoloration.

Exploratory objective: To assess the impact of NTP treatment on cancerous and normal tissues.
Exploratory endpoint: Evidence of cancer cell death and absence of normal tissue degradation in samples treated with NTP ex vivo or in situ. The exploratory objective (to assess the impact of NTP treatment on cancerous and normal tissues) will be assessed through the analysis of treated and untreated tissues.

### Subject selection

This trial will be conducted in compliance with the protocol, the ethical principles that have their origin in the Declaration of Helsinki, good clinical practice (GCP), ISO 14155:2020 and Health Canada Medical Devices regulations. Any questions about eligibility criteria must be addressed prior to patient registration.

#### Inclusion criteria

Age ≥ 18 years at the time of signing the study consent form.ECOG ≤ 2.Patient with cT1-4 breast cancer for groups A and B; patient with cT1/cT2 breast cancer (based on physical examination, not radiological measurements) for group C. Histological diagnosis must be invasive ductal carcinoma of the breast. 2. Patients are staged per standard of care practice. Patients with the eligible T stage cancers of any N or M stage are eligible.The patient is scheduled to undergo a lumpectomy.

#### Exclusion criteria

Prior treatment for the tumor of interest (including chemotherapy, immunotherapy, or radiotherapy).Patient planning or undergoing intraoperative radiotherapy.Diabetes (types I and II).Hypercortisolism.Collagen vascular disease.Patient requiring systemic corticosteroids at physiologic doses exceeding 10 mg/day of prednisone or its equivalent.Patient receiving daily chemotherapy for rheumatological conditions.Pregnancy (a urine pregnancy test must be obtained for nonsterile women of childbearing potential prior to surgery).

### Study investigational medical device – convertible plasma jet

The NTP source used for this trial is the Convertible Plasma Jet (CPJ) from NexPlasmaGen, Inc. A complete description of this NTP applicator can be found in patents No. US 2007/0029500 A1 and US 2022/0353982 A1, as well as in Boisvert et al. [27]. The CPJ is considered a Class III medical device per Health Canada regulations.

Briefly, the electrode configuration of the CPJ device is a coaxial configuration in which a dielectric material separates the ground electrode and the annular open gap for the flowing gas. A quartz tube acts as the dielectric barrier and is placed directly inside the grounded tube, thus leaving an annular gap for gas injection between the dielectric and the central powered tube electrode. The whole assembly forms a dielectric barrier discharge configuration 3 cm in length. As the high-voltage electrode is hollow, the NTP-forming gas can be injected either through it or through the annular gap [27].

With the CPJ, it is possible to sustain three different discharge modes (Ω; 𝛾 and jet modes) when a 13.56 MHz sinusoidal excitation waveform is fed to the high-voltage electrode. For this study, all the treatments will be performed at atmospheric pressure (101.3 kPa) with helium (99.999% purity) injected within the annular gas gap between the dielectric and the hollow high-voltage electrode and with oxygen (medical grade) injected within the high-voltage electrode. The discharge mode used will be the 𝛾 mode.

### Rationale for the starting dose and dosing schedule

The dose of NTP produced by the CPJ is described by the duration (min) of the treatment. Based on the in vivo studies performed with the CPJ V4.4, the maximum dose used will be 5 min of treatment at 13 W (0 Hz, 100% DC), 5000 sccm helium and 25 sccm O_2_ per 7 mm^2^. This dose has proven to be efficacious and safe in mice (*manuscript in preparation*). For V5 (clinical version) of the CPJ, by comparing the physical, electrical and thermal properties of V4.4 and V5, the equivalent conditions were found to be 220 V, 100 Hz, 80% DC, 5000 sccm helium and 20 sccm O_2_ in the capillary, with stationary treatment for 5 min per 7 mm^2^. This dose will be defined as the highest dose assessed in this trial, dose 3 (Table 1). The dose will not be increased above this mark in search of the maximum tolerated dose (MTD), as it would not necessarily be associated with improved treatment efficacy (probably due to the increase in temperature that accompanies the increase in applied power). Instead, the maximum dose used in this study will be the dose that has been found to be efficacious (i.e., dose 3) in vivo or lower in the presence of dose-limiting toxicities (DLTs). A DLT is defined as any of the following attributable to NTP administration (definitely, probably, or possibly) occurring after NTP administration until the 1-week post-op follow-up visit:

Fever; grade 4,Breast infection; grade 4,Skin ulceration; grade 4,Chest wall necrosis, grade 4.

**Table 1 Tab1:** Doses used in the breast cancer PAINT first-in-human investigation

Dose Level #	Dose	Group
**Dose Level − 1**	**2 min per 7 mm** ^**2**^	**Group C – if 1 DLT out of 3 or 2 DLTs out of 6 (30 min max)**
Dose Level 1 (starting dose)	3 min per 7 mm^2^	Group C, Cohort 1 (30 min max)
Dose Level 2	4 min per 7 mm^2^	Group C, Cohort 2 (30 min max)
Dose Level 3	5 min per 7 mm^2^	Group C, Cohort 3 (30 min max) Group A (15 min max) Group B (15 min max)

Three dose levels will be assessed for DLTs. If DLT toxicity occurs in the initial cohort for group C, then a provision has been added for a fourth lower dose to be explored with an expanded patient cohort (in bold text)

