### Treatment plan

The minimum number of patients required to complete this first-in-human study will be 9, and the maximum sample size for the study will be 30. At the end of each group/cohort, a safety cohort review will be performed to analyze the safety data and approve the transition to the next group/cohort if applicable.

The study will be conducted at the CHUM site in Montreal, Quebec.

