#### Group B (*n* = 3)

Three patients in group B will then be enrolled concurrently and treated with NTP, also concomitantly, as none of the NTP-treated tissues will be left inside the patients. Group B will then be closed to enrollment until safety assessment of all three subjects is performed at post-op follow-up #2. Safety will be confirmed if none of the three patients experience DLTs (Fig. 1).NTP treatment of part of the tumor bed in situ at dose level 3 (5 min per 7 mm^2^) for a maximum of 15 min (i.e., treatment of 21 mm^2^). During surgery, part of the tumor bed will be treated with NTP inside the patient. The treated tumor bed will be removed from the patient immediately after NTP treatment and analyzed as part of this clinical protocol. Part of the tumor removed during surgery will be sent to the PW laboratory for treatment with NTP at dose 3 and analysis as part of this clinical protocol. The rest of the tumor and tumor bed will be sent to pathology as part of the SOC procedures. No treated tissue will stay inside the patient.

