#### Group C (*n* = 6–24)

After safety is confirmed for group B, group C patients will be enrolled based on the 3 + 3 dose escalation rule up to a maximum dose level of 3 (Table 1). Even if the safety of dose 3 is confirmed in group B, the first patient cohort treated in group C will receive a lower starting dose of 3 min per 7 mm^2^ (dose 1) (Table 1). In cohort 1, at dose level 1, the first patient will be enrolled and treated with NTP. After follow-up #2 one-week post-op, only if there was no DLT in the first patient could accrual be reopened to enroll the second and third patients in the cohort. Subjects will be enrolled in cohorts of three each. If no DLT is encountered in any of the 3 subjects after 1-week post-op, dose escalation according to Fig. 2 will be allowed. If one of the 3 subjects experiences a DLT, three additional subjects will be enrolled at the same dose level, and if none of these 3 additional subjects experience a DLT, dose escalation will be allowed. A safety cohort review will be conducted after the patients in each cohort complete the 1-week post-op follow-up visit. The MTD will be defined as the next lower dose level below the one in which > 1/3 of the subjects or ≥ 2/6 of the subjects experience DLT. Up to 6 additional subjects may be enrolled at the MTD to obtain additional data on the safety and efficacy of the product. If escalation to dose level 3 is reached and < 1 out of 6 subjects experience DLT, dose escalation will stop, and 6 additional subjects will be enrolled at dose level 3 to obtain additional data on the safety and efficacy of the product.

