### Study calendar

The details of the visits associated with this study and their content can be found in Table 2.

**Table 2 Tab2:** Study calendar

Required Investigations	Screening	Day of Surgery and NTP treatment	Post-op Follow-Up #1^1^	Post-op Follow-Up #2	Post-op Follow-Up #3	End of study Follow-up	
Window	Within 28 days of treatment	-	Day 2–3 post-op	Day 7 post-op; +/- 3 days	Day 30; +/- 7 days	Day 90; +/- 30 days	
Demographics	X						
History and Physical Exam	X	X	X	X	X	X	
Quality of life questionnaire	X^2^		X	X	X	X	
Hematology, Biochemistry	X				X	X	
NTP administration and Tissue collection		X					
Ultrasound	X				X		
Image collection	X^3^			X	X	X	
ECG	X						
Concomitant medication review	X	*Continuously*					
Adverse events	*Continuously*						

^1^ Post-op follow-up #1 can be conducted by phone. If so, only ECOG performance status and quality of life questionnaires will be mandatory

^2^ Not applicable for group A

^3^ Image collection for group C patients only

The follow-up period covers 3 months and is divided into 4 follow-up visits or calls. The first follow-up visit is at 2–3 days post-op, with a physical exam and a QOL questionnaire (custom-made for this study). The second follow-up is at 7 days post-op, with a physical exam and a QOL questionnaire for groups B and C, and the image collection for group C only. The third follow-up is at 30 days post-op, with a physical exam, a QOL questionnaire, blood tests (hematology and biochemistry), ultrasound and image collection. The last follow-up is at 90 days post-op, with a physical exam, a QOL questionnaire, blood tests (hematology and biochemistry) and image collection. Group A (ex vivo only) does not have to attend any follow-up visits (Fig. 3a). The participation of group B in this study stops after follow-up #2 (Fig. 3b). Patients in group C must attend all the visits (Fig. 3c).

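### The DLT period ends at a visit allowed on day 4 to day 10, so a listed, attributable grade 4 event within the first week can fall outside the DLT count

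*Protocol article*

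**What the plan says.** The section on the rationale for the starting dose lists four DLTs, all grade 4 (fever, breast infection, skin ulceration, chest wall necrosis). They must be at least possibly attributable to NTP and fall in the period "occurring after NTP administration until the 1-week post-op follow-up visit". The end point is a visit, not a day. Table 2 sets the window of that visit, post-op follow-up #2, at "Day 7 post-op; +/- 3 days".

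The decisions that use the visit or the DLT count are:

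- **Primary endpoint (Objectives):** "All patients that receive the treatment and complete the 1-week follow-up visit will be evaluated for acute toxicity".
- **Group B:** "Group B will then be closed to enrollment until safety assessment of all three subjects is performed at post-op follow-up #2". Safety is confirmed if none of the three has a DLT. The Study calendar then ends Group B participation after that visit.
- **First Group C patient:** "After follow-up #2 one-week post-op, only if there was no DLT in the first patient could accrual be reopened".
- **Escalation:** "If no DLT is encountered in any of the 3 subjects after 1-week post-op, dose escalation according to Fig. 2 will be allowed". With one DLT in three, three more patients must be free of DLTs.
- **Cohort review (Group C section):** "A safety cohort review will be conducted after the patients in each cohort complete the 1-week post-op follow-up visit". Its remit, in the Treatment plan, is that "a safety cohort review will be performed to analyze the safety data and approve the transition to the next group/cohort if applicable".

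Table 2 records adverse events continuously. The next Group C visit after follow-up #2 is on day 30, plus or minus 7 days.

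**The concern.** A visit window is ordinary scheduling tolerance when it only moves an assessment. Here it also sets the length of the DLT observation period, because the definition stops at the visit. Two patients at the same dose with the same event on the same day can be classified differently because one was seen earlier.

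The DLT count drives the 3+3 rule, the Group B gate and the first-patient hold in a first-in-human study. Each level has 3 or 6 patients, so one event can change the decision. The first-patient hold rests on one person and states no criterion other than DLTs. No section sets a minimum observation time before any of these gates may open.

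**Working it through.** **Inputs from the protocol.** DLT period: to follow-up #2. Window: day 7 ± 3. Next Group C visit: day 30 ± 7. Escalation rule: 0 of 3, or 1 of 3 followed by 0 of 3. The protocol gives no DLT rate or onset distribution and no operating characteristics, so there is no figure of its own to reproduce.

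**Window arithmetic.**

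- Earliest visit 7 − 3 = day 4; latest 7 + 3 = day 10; ratio 10/4 = 2.5.
- A day-4 visit leaves out 3 of the nominal 7 days, 3/7 = 43%.
- The next scheduled Group C visit is day 23 to day 37, that is 23 − 4 = 19 to 37 − 4 = 33 days after a day-4 visit.

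**Does other text close the gap?** The escalation sentence speaks of the time after 1 week post-op. That can delay escalation, but it does not make an event after the visit a DLT. The cohort review and the acute-toxicity evaluation are tied to the visit itself.

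**Illustration (assumed).** Let P be the 7-day risk of a listed, attributable event, with constant daily risk through day 10. A patient seen on day d then has DLT probability q = P·d/7. The figures use the DLT count alone, before any action by the cohort review.

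*First patient seen on day 4, cleared, then a qualifying event on days 5 to 7:* 3P/7. At P = 10% this is 0.30/7 = 4.3%.

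*Meeting the 3+3 rule:* Pr(0 of first 3) + Pr(1 of first 3) × Pr(0 of next 3). If all patients share q, this is (1 − q)³ + 3q(1 − q)⁵.

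At P = 10%:

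- All on day 7, q = 0.100: 0.729 + 0.177 = 0.906.
- All on day 4, q = 0.057: 0.838 + 0.128 = 0.966.
- All on day 10, q = 0.143: 0.630 + 0.198 = 0.828.
- One of the first three on day 4, the rest on day 7: Pr(0 of 3) = 0.9² × 0.943 = 0.764; Pr(1 of 3) = 2 × 0.1 × 0.9 × 0.943 + 0.057 × 0.9² = 0.216; total 0.764 + 0.216 × 0.729 = 0.921.

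| P | First patient, 3P/7 | All day 4 | All day 7 | All day 10 | One early visit | Change from all day 7 (points) |
|---|---|---|---|---|---|---|
| 2% | 0.9% | 99.9% | 99.5% | 99.1% | 99.6% | +0.08 |
| 5% | 2.1% | 99.1% | 97.3% | 94.9% | 97.8% | +0.45 |
| 10% | 4.3% | 96.6% | 90.6% | 82.8% | 92.1% | +1.50 |
| 20% | 8.6% | 88.2% | 70.9% | 52.4% | 74.9% | +4.08 |

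*Visit days independent and uniform on days 4 to 10:* the mean day is 7, so the average q equals P and the chance of meeting the rule is the same as with all visits on day 7 (90.6% at P = 10%).

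**The case against.** The strongest reply is that this is a wording point with ample safeguards.

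- **The event is not lost.** In Group C, adverse events are recorded continuously, and the Abstract names serious adverse event reports as a safety source. The cohort review looks at the safety data as a whole and must approve each transition, and the escalation sentence only allows escalation. This stands. A reader might infer from the 19 to 33 days to the next visit that nobody would see the event; the documents do not support that. What is lost is the DLT label. Even so, the review may follow directly on an early visit, and the first-patient hold is worded in DLTs alone.
- **The hold reopens accrual, not treatment.** An event on days 5 to 7 may well surface before the second and third patients are treated. This also stands, though no minimum interval is stated.
- **Group B carries little risk.** All treated tissue is removed, and Group C starts at a lower dose. This limits the consequence but does not alter the classification.
- **The assumed risks may be too high.** Only four grade 4 events qualify. The Background says that NTP has not been associated with severe adverse events, and the Discussion describes a 20-patient trial without attributable events. Those results come from other devices, so they do not establish a low rate here, but the 10% and 20% rows are illustration only. Front-loaded onset would shrink the 43% loss; later onset would enlarge it.
- **A one-week gate was plainly intended.** The Study calendar text places follow-up #2 at 7 days. That supports the fix, but it does not change the DLT definition as written.

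**Conclusion.** The inconsistency is real and follows from two stated items, the DLT definition and the visit window. A listed grade 4 event attributable to NTP that occurs after an early visit but within 7 days is not a DLT. It therefore does not count for the first-patient hold, the Group B gate or the 3+3 rule.

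Its weight is minor to moderate. With one early visit among the first three patients, the chance of meeting the escalation rule rises by 0.08 to 4.08 percentage points over assumed 7-day risks of 2% to 20%. Shifts such as 90.6% to 96.6% at P = 10% need every visit on day 4, and nothing in the protocol suggests that pattern. All these figures rest on assumed risks and constant daily onset.

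Two stronger readings are tempting. One is that the plan is biased towards escalation. It is not shown to be: late visits add capture, and with visit days independent and symmetric about day 7 the average chance is unchanged. The other is that any grade 4 event is at issue. Only the four listed events can be DLTs, whatever the visit day.

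**What to change.** Count DLTs through day 7 or follow-up #2, whichever is later. Either set the follow-up #2 window to day 7 to day 10, or require a phone DLT enquiry on or after day 7 when the visit is earlier. Allow no accrual reopening, Group B clearance or cohort review before that point for each patient concerned. Align the Objectives, the DLT definition, the Group B and Group C sections and Table 2.

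**Cost.** Gates move by up to 3 days (from day 4 to day 7), with at most one extra phone contact per patient; Table 2 already accepts a phone contact for follow-up #1. A spread of 7 to 10 days remains (10/7 = 1.43-fold). Escalation becomes slightly more cautious because capture is only added. With visit days uniform on 4 to 10, the mean DLT period becomes (4 × 7 + 8 + 9 + 10)/7 = 7.86 days. At P = 10% this gives q = 0.1 × 7.86/7 = 0.112, and the chance of meeting the rule is 0.700 + 0.186 = 88.5%, against 90.6% now.

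**Alternatives.** A strict day-7 cut-off would drop day 8 to 10 events that now count before a late visit (3P/7 for a patient seen on day 10, 4.3% at P = 10%). A common day 10 would remove the spread, but it moves gates by up to 6 days and gives 82.8% against 90.6% with all visits on day 7 at P = 10%. That is a debatable design choice and is not needed to repair this point.

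### The DLT list is set at exactly grade 4, so a fatal listed event literally adds nothing to the DLT count, and attributable grade 3 events reach the dose decision only through review judgement

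*Protocol article*

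**What the plan says.** **DLT definition** (Rationale for the starting dose and dosing schedule). A DLT is any of four events judged definitely, probably or possibly attributable to NTP, from administration to the 1-week visit: "Fever; grade 4,Breast infection; grade 4,Skin ulceration; grade 4,Chest wall necrosis, grade 4". The list is closed. The same section sets the top dose at the one found efficacious "in vivo or lower in the presence of dose-limiting toxicities (DLTs").

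**Rules that count DLTs.**
- Group B: "Safety will be confirmed if none of the three patients experience DLTs".
- Group C: accrual reopens after the first patient of cohort 1 only without a DLT. Escalation is allowed after 0/3, or after 1/3 followed by 0/3. The MTD is the level below one in which more than 1/3, or at least 2/6, of subjects have a DLT.
- Table 1: dose level -1 is triggered by DLT counts.

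**Primary endpoint** (Objectives). Through the 3 + 3 design, "a safe and tolerable dose of NTP in patients with breast cancer will be determined". The paragraph continues: "The adverse effects of NTP produced by the CPJ will be assessed based on DLTs, AEs, physical exams, quality of life (QOL) questionnaires", and adds clinically significant laboratory changes.

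**AESIs** (Objectives, secondary endpoints). Recorded throughout the study are "Fatigue; grade 3,Breast pain; grade 3,Skin ulceration; grade 3,Chest wall necrosis; grade 3,Breast atrophy; grade 3", plus three ungraded cosmetic or texture items.

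**Review** (Treatment plan). At the end of each group or cohort, "a safety cohort review will be performed to analyze the safety data and approve the transition to the next group/cohort if applicable". The abstract likewise takes a wide view: "The safety and tolerability of treatment will be evaluated by means of dose-limiting toxicity, adverse event (AE) and serious adverse event reports", with examinations and laboratory evaluations.

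**The concern.** In a rule-based escalation the DLT definition is the measuring instrument: whatever it leaves out cannot move a count. Here it has two gaps of unequal weight.

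The first is at the top of the scale. AEs are graded by CTCAE v5.0, on which a fatal event is grade 5. A list that says grade 4, with no *or higher* and no death clause, literally excludes the worst form of the very events it names. At stake is whether a first-in-human trial's gates respond to a treatment-attributed death by rule or only by judgement.

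The second lies just below the threshold. Skin ulceration and chest wall necrosis appear on both lists, at grade 4 as DLTs and at grade 3 as AESIs. At grade 3 they are recorded, but no stated rule counts them. The claim to be made at the end is a safe and tolerable dose, which is broader than a dose with few grade 4 events of four kinds in one week.

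**Working it through.** No toxicity rate is given in the documents and none is needed. The check applies the printed rules to defined cases.

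**Inputs.** DLT list and window, and the Table 1 trigger: Rationale for the starting dose and dosing schedule. Gate: Group B. Escalation and MTD rules: Group C. AESI list and CTCAE v5.0: Objectives. Assumption: grade 5 means death, as that scale uses it.

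**Step 1. Is the missing *or higher* a printing loss?** Unlikely. The sign ≥ is printed in the inclusion criteria (age) and in the MTD definition. All four DLT terms carry the bare grade.

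**Step 2. Fatal listed events within the window, attributed to NTP.**

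| Case | As printed | With *grade 4 or higher* |
|---|---|---|
| Group B, 1 of 3 fatal | 0/3: condition for confirmed safety met | 1/3: not met |
| Group C cohort 1, first patient fatal | 0/1: condition to reopen accrual met | 1/1: not met |
| Group C, 1 of 3 fatal | 0/3: escalation allowed | 1/3: three more at the same level |
| Group C, 2 of 3 fatal | 0/3: escalation allowed | 2/3, above 1/3: MTD threshold crossed |
| Group C, one grade 4 in the first three, one fatal in the next three | 1/6: escalation allowed | 2/6: MTD threshold crossed |

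The last row shows that the gap can matter even when the count is working: 1 + 0 = 1 of 6 as printed, against 1 + 1 = 2 of 6.

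**Step 3. Attributable grade 3 events.** If 3 of 3 patients in a cohort had attributable grade 3 chest wall necrosis, the count would be 0/3 as printed and still 0/3 with *grade 4 or higher*. The wording fix does not touch this case. It reaches the dose decision only through the safety cohort review, for which the text states no criterion on non-DLT events.

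**Step 4. What the text does link to the dose.** The primary endpoint paragraph names AEs, examinations, QOL and laboratory changes beside the DLTs. The review must approve each transition. After the last level there is no further transition to approve, and the only ground stated for a top dose below dose 3 is DLTs.

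**Step 5. Sample size.** Groups A, B and C give 3 + 3 + 24 = 30 at most, which agrees with the stated maximum. Neither change alters it.

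**The case against.** **The bare grade is meant as a threshold.** The AESI list uses the same notation. Read equally literally, grade 4 chest wall necrosis would not be an AESI, which is implausible. This stands as to intent: the DLT list very probably means grade 4 or higher. A fatal event might also be scored at grade 4 before death, although the article does not say how a worsening event is counted. Neither argument is a reason to leave a decision threshold open to two readings.

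**Other safeguards exist.** Serious adverse event reporting and the cohort review would be expected to catch a death, and the DLT rules only *allow* escalation. This also stands. A reader might infer that the trial would escalate past a death; the documents do not support that, because the review must approve the transition.

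**Grade 4 for the count and grade 3 for monitoring is a coherent two-tier scheme.** Accepted as a design choice. The review's criteria may sit in the full protocol, and Fig. 2, whose caption mentions acceptance criteria, is not shown. So the grade 3 point concerns how the final dose is described. It is not a claim that grade 3 events must be DLTs.

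**Stronger readings that fail.** A reader might infer that a level with 0 DLTs but serious other toxicity would qualify as the MTD. It would not: the MTD exists only relative to a higher level that crossed the DLT threshold. Nor is tolerability judged on DLTs alone, since the primary endpoint names wider assessments. Finally, one might wish to calculate how often grade 3 events would stop a level. The documents give no such rate, and counting those events as DLTs is not proposed here.

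**Conclusion.** The point holds in a limited form. As printed, the closed DLT list excludes a fatal listed event from every stated count, and in the cases above this changes the outcome of the Group B gate, the first-patient gate, escalation and the MTD threshold. The practical risk is small, because intent and oversight both point the other way. The defect nevertheless sits in the definition on which all the counts depend, and it is almost free to correct.

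The secondary point is narrower. Attributable grade 3 skin ulceration or chest wall necrosis enters no stated count and bears on the dose only by the review's judgement. That can be defended for escalation. It does not by itself support describing the dose named at the end as safe and tolerable.

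The conclusion assumes that grade 5 denotes death and that the article prints the DLT definition in full. If the full protocol already says grade 4 or higher, the first part reduces to correcting the article.

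**What to change.** 1. Write *grade 4 or higher* for each of the four DLT terms, or add *any NTP-attributable grade 5 event* to the list.
2. State that the final dose will be reported as safe and tolerable only after NTP-attributable grade 3+ events and AESIs, tabulated by dose level, have been weighed. Otherwise report it as the highest level not exceeding the listed-DLT threshold, with tolerability described separately.

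**Cost.** Wording only; no added patients, visits or assessments. The downside is that the dose claim may be slightly narrower.
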